##### Overview

###### Measures

Outcomes of WP 2 include measurements of cardiorespiratory fitness, muscle strength, power, and muscular endurance. Norway (Oslo and Bergen) and Switzerland (Basel) will participate in WP 2 (Table 1 provides an overview of tests and self-reported measures performed at each site specific to WP 2). In Norway, age- and sex-matched controls will be the same-age friend or sibling of the survivor of childhood cancer, chosen and invited by the survivors of childhood cancer themselves. In Switzerland, age- and sex-matched controls will be recruited from siblings or friends of survivors or within the network of the Swiss PACCS study team.

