**Figure 1 figure1:**
[figure not shown]
Overview of the objectives and methods for the 4 work packages (WPs) of the Physical Activity and Fitness in Childhood Cancer Survivors study.

We aimed to include a minimum of 500 survivors of childhood cancer aged 9 to 16 years in WP 1. We aimed to consecutively enroll approximately 150 participants from WP 1 to WP 2. The age group in WP 2 will be 9 to 18 years, as 1 to 2 years may, in some sites, elapse from inclusion into WP 1 to participation in WP 2. In addition, in WP 2, 150 age- and sex-matched controls will be enrolled. A subsample of 40 selected WP 1 participants and one of their parents will be invited to participate in qualitative interviews in WP 3. Participants will be purposely sampled to maximize the variation of key sociodemographic and clinical factors, including activity levels and rural or urban places of residence. Approximately 10 school nurses and 10 physical education teachers will also be recruited. In WP 4, around 30 survivors of childhood cancer aged 12 to 18 years within the lowest tertial of total PA, as assessed by the accelerometer in WP 1, without contraindications for vigorous PA, will be recruited among the participants of WP 1. As WP 4 is a pilot feasibility study, we aim to recruit survivors of different diagnoses, age ranges, and genders. All countries and study sites will participate in WP 1; Norway and Switzerland will participate in WP 2; Norway and Denmark will participate in WP 3; and Norway, Finland, and Germany will participate in WP 4.

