##### Data Management

Study data will be collected and managed using REDCap (Research Electronic Data Capture) electronic data capture tools hosted at the Norwegian School of Sport Sciences [66,67]. REDCap is a secure, web-based software platform designed to support data capture for research studies. Data from all sites will be entered by the study sites independently in REDCap.

##### Power Calculation and Statistical Analyses WP 2

Sample size calculations and power assessment were based on VO_2_peak. On the basis of results from international studies, we expect to find a difference of 10% between survivors of childhood cancer and controls [22]. To detect a difference of 10% in VO_2_peak between survivors and healthy controls, with a statistical strength of 80%, the study needs to include 23 survivors of childhood cancer. The same number of patients are needed to get the same statistical power for the strength tests assuming a difference of 10%. Owing to heterogeneity between diagnostic groups and the need for subgroup analysis (diagnosis, age, and gender), we plan to include 150 survivors as we expect the group size to be as small as 30 participants.

We will use descriptive statistics to present the current PF, physiological determinants of PF, and PA of survivors of childhood cancer compared with controls. We will use multilevel (mixed) linear models to compare PF and PA between survivors of childhood cancer and controls and include an interaction term (for instance, age group, gender, and diagnosis) to identify differences in physiological determinants between survivors of childhood cancer and controls. All analyses will be adjusted for the study site by including sites as random intercepts in the mixed models. Where available and depending on the research question, the fitness outcomes will be transformed into *z* scores according to the norm data. Depending on the outcome, we will perform univariable and multivariable mixed logistic, linear, or ordinal regression models to identify clinical and physiological factors associated with PF in survivors.

#### WP 3

The outcomes of WP 3 include facilitators of and barriers to PA. Norway (Oslo and Bergen) and Denmark (Copenhagen) will participate in WP 3.

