###### Quantitative Data

As this is a feasibility study, we will mainly use descriptive statistics to present the study results. We will use numbers and proportions to describe categorical variables and means, SDs (or median and IQR if the data are skewed), and ranges to describe continuous variables. *P* values will be calculated based on appropriate univariable and multivariable models depending on the outcome and adjusted for the study site by introducing a random intercept (mixed model). *P* values are interpreted as flagging trends and not as hypothesis tests.

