## Results

Research activity for this study commenced in November 2016 with the piloting of questionnaires and recruitment to WP 1 at the Oslo, Norway site. The project received funding from the Research Council of Norway for the period from June 2018 to June 2022. International collaboration was established after June 2018. Data collection at all sites was initiated by October 2020 for WP 1 and concluded on January 2021, with 517 survivors of childhood cancer included. Data cleaning and analysis are currently underway. A total of articles are under preparation for publication. Data collection for WP 2 was initiated in January 2019 and concluded in December 2020, with 157 survivors of childhood cancer and 113 controls included. Data cleaning and analysis are currently being conducted. A total of 6 articles are planned based on the WP 2 data set. Data collection for WP 3 was initiated in January 2018. Patient and parent interviews were concluded in July 2020, with 63 survivors of childhood cancer and 68 parents. Interviews with local stakeholders were initiated in January 2020 and concluded in October 2020, with a total of 18 participants interviewed (teachers, special needs teachers, and school nurses). Data from the patient and parent interviews have been analyzed and are currently being written for publication. A total of 2 articles have been published as of January 2022 [81,82], and 2 more are under preparation for publication. Data from interviews with local stakeholders are currently being analyzed, and 1 article is planned. WP 4 recruitment was initiated in May 2021 and is still ongoing as of January 2022. The study is planned to be completed by July 2022. As of January 2022, 23 survivors of childhood cancer have been included, of which 11 have completed the intervention. Detailed plans for data analyses for WPs 1 to 4 are described in the "Assessments, Power Calculations, and Statistical Analyses" section.

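### WP 2 links Norwegian controls individually to survivors, but its survivor-control model names only a site random intercept and does not commit to age and sex adjustment, so standard errors are too large if pair members are alike

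*Protocol article*

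**What the plan says.** The WP 2 Measures section sets out where the controls come from. In Norway, "age- and sex-matched controls will be the same-age friend or sibling of the survivor of childhood cancer", and the survivor picks and invites that person. In Switzerland, matched controls may be siblings or friends of survivors, or may be found "or within the network of the Swiss PACCS study team". The Methods section on study population gives the planned number: "In addition, in WP 2, 150 age- and sex-matched controls will be enrolled", against about 150 survivors. The Results section reports that WP 2 closed "with 157 survivors of childhood cancer and 113 controls included".

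The analysis is under Power Calculation and Statistical Analyses WP 2. The main comparison reads: "We will use multilevel (mixed) linear models to compare PF and PA between survivors of childhood cancer and controls". Clustering is handled by one statement: "All analyses will be adjusted for the study site by including sites as random intercepts in the mixed models". No pair, family or matched-set term is mentioned. Age group and gender appear only as examples of interaction terms. Conversion of fitness outcomes to z scores is conditional on norm data being available and on the research question.

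**The concern.** A control who is a survivor's sibling or self-chosen friend, of the same age and sex, is likely to resemble that survivor in fitness and activity. The design therefore creates matched sets within site, and the stated model has no level for them. A model that treats the two members of a pair as independent, given site, adds their variances and ignores the covariance that cancels in the difference. If the covariance is positive, the reported standard error is too large.

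The cost is needlessly wide confidence intervals and reduced power for the survivor-control contrast. It matters most where the plan has least room: the interaction terms and the diagnosis, age and gender subgroups, which the plan expects to be as small as 30.

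The second part concerns balance. Complete 1:1 matching would equalise age and sex between the groups by design. Enrolment did not end 1:1, so over ages 9 to 18 the main comparison needs age and sex in the model rather than relying on the matching.

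**Working it through.** **The plan's own figure.** The WP 2 section gives 23 survivors for a 10% difference in VO2peak at 80% power. It gives no SD, significance level or sidedness, and does not say whether the calculation is paired. The 23 fits an unpaired comparison with 23 per group if the SD is about 12.1% of the mean (two-sided 5%) or 13.6% (one-sided 5%). It equally fits 23 pairs if the SD of the paired difference is about 17.1% or 19.3%. It can be neither confirmed nor refuted, and it does not show whether pairing was intended.

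**Inputs.** n1 = 157 survivors and n2 = 113 controls (Results). Number of pairs m = 113, an assumption that every control is linked to one survivor. Within-pair correlation rho is not given; 0.1, 0.3 and 0.5 are assumed. Outcome variance is set to 1, since only ratios matter.

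**Unmatched survivors.** 157 − 113 = 44, the minimum under 1:1 matching.

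**Standard error reported without a pair term.** sqrt(1/157 + 1/113) = sqrt(0.01522) = 0.1234.

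**True standard error of that same difference.** The variance is 1/157 + 1/113 − 2·m·rho/(157·113), which with m = 113 is 0.01522 − 2·rho/157.

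**Standard error with a pair effect (generalised least squares).** Let A = m/(1 − rho²) + (n1 − m), C = m/(1 − rho²) + (n2 − m) and B = m·rho/(1 − rho²). The variance of the difference is (A + C − 2B)/(AC − B²). For rho = 0.3: A = 168.18, C = 124.18, B = 37.25, so the variance is 217.85/19,496 = 0.01117 and the standard error is 0.1057.

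| rho | Reported SE | True SE, same difference | Pair-model SE | Reported/true | Reported/pair model | Actual two-sided type I error at nominal 5% |
|---|---|---|---|---|---|---|
| 0.1 | 0.1234 | 0.1181 | 0.1180 | 1.05 | 1.05 | 4.1% |
| 0.3 | 0.1234 | 0.1068 | 0.1057 | 1.16 | 1.17 | 2.4% |
| 0.5 | 0.1234 | 0.0941 | 0.0907 | 1.31 | 1.36 | 1.0% |

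**Fewer linked controls.** With 75 of the 113 controls linked, reported/true falls to 1.10 at rho 0.3 and 1.18 at rho 0.5, and reported/pair model to 1.11 and 1.25.

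**Simulation check (300 runs per setting, 157/113, three sites).** At rho 0.4 the site-only mixed model had a mean SE of 0.122 against an empirical SD of 0.104, with type I error 0.7%. With a pair intercept, and site as a fixed effect, the mean SE was 0.098 against an empirical SD of 0.1005, with type I error 6.7%. Monte Carlo error on the type I rates is roughly 1 to 1.5 points.

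**Age and sex.** An interaction of group with age group or gender would normally bring those main effects into that particular model, and z scores would normally remove much age and sex variation. Both provisions are conditional, and neither is tied to the main survivor-control comparison.

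**The case against.** The strongest defence is that the plan says how site is handled and does not say that site is the only random effect. This is a condensed article, and a fuller analysis plan could add a pair term. That limits the severity, but it does not remove the point: the article goes as far as specifying the random-effects structure of this comparison, and that structure leaves out a level its own recruitment creates.

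Three further objections stand and set the size. Some Swiss controls may have no tie to any survivor. The correlation is assumed, and the part due to age and sex matching would shrink after adjustment. The error is conservative.

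Four stronger readings are tempting, and the documents do not support them:

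- **False positives.** A reader might infer that ignoring the pairs inflates significance. With positive correlation the opposite holds.
- **A large loss of information.** Comparing the reported SE with the pair-model SE suggests 27% to 46% of the information is lost at rho 0.3 to 0.5. Most of that is over-wide intervals. The unpaired difference itself is less efficient than the pair-model estimate by only about 2% (1 − (0.1057/0.1068)²) to 7% (1 − (0.0907/0.0941)²).
- **A demonstrated imbalance.** Having 44 or more unmatched survivors removes the guarantee of balance. It does not show that the groups differ in age or sex.
- **The same fault in WP 4.** WP 4 remeasures each child, and its models are "adjusted for the study site by introducing a random intercept (mixed model"). But that section is mainly descriptive, leaves the model to suit the outcome, and treats P values as flags for trends. A within-child change analysis with a site intercept already fits the text.

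**Conclusion.** The point holds for WP 2. The stated survivor-control model names site as its only random intercept, although Norwegian controls, and possibly some Swiss ones, are individually linked to survivors. Fitted as written, it would overstate the standard error by about 5% to 31% for rho between 0.1 and 0.5, if all 113 controls are paired and pair members are positively correlated. The overstatement is smaller with fewer linked controls or after age and sex adjustment. It does not threaten a false claim of difference; it weakens intervals and power, chiefly in subgroups and interactions. Separately, with 157 survivors and 113 controls, matching alone cannot be relied on to balance age and sex, and the plan does not commit the main comparison to adjusting for them. This is worth correcting because a better model is available at almost no cost, not because a main conclusion is shown to be at risk.

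**What to change.** In the WP 2 analysis text:

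- Keep a matched-set identifier tying each survivor to their own friend or sibling.
- Add a matched-set random intercept beside the site intercept in the survivor-control comparison. Treat unmatched survivors and unlinked Swiss controls as sets of one, so that nobody is dropped as a strictly paired analysis would require.
- Include age and sex as main effects in that comparison, whether or not interaction terms or z scores are also used.
- Report how many controls were linked to a survivor, by site.

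Regressions among survivors only are unaffected by the pairing. The cost is a change of model wording and code, plus one identifier in the data set. No new participants or measurements are needed, and the article describes WP 2 data cleaning and analysis as still in progress.

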###### Cardiorespiratory Fitness

Before testing, survivors of childhood cancer will undergo a cardiological screening. Peak oxygen uptake (VO_2_peak) will be assessed using a cardiopulmonary exercise test (CPET). In Norway, the CPET will be performed by walking and running on a treadmill using a child-friendly continuous graded treadmill protocol until exhaustion [48], whereas in Switzerland, the CPET will be performed on a cycle ergometer using an incremental bike protocol from Godfrey [49]. The starting workload after habituation to the treadmill will be 3.0 km/hour at 0% inclination. The workload will then be increased every minute by alternately increasing the speed by 1 km/hour and the inclination by 2% every other minute. For the bike protocol, the initial workload will be set to 10, 15, or 20 W depending on the child’s height and increased by 10, 15, or 20 W every minute, respectively. The participants will be encouraged to keep a pedaling frequency of 60 to 90 revolutions per minute. Gas exchange and ventilatory variables will be measured continuously, breath by breath, using a Hans Rudolph 2-way breathing mask (Hans Rudolph). Peak heart rate will be measured through a 12-lead electrocardiogram, and blood pressure and transcutaneous oxygen saturation will be measured after 5 minutes of rest in the sitting position, during the test, and shortly after termination. The Borg rating [50] of perceived exertion will be assessed at the end of the test. The VO_2_peak is defined as the highest oxygen consumption value sampled over a 30-second interval. The ventilatory threshold will be calculated using the ventilatory equivalent method, expressed as oxygen uptake (VO_2_). The minute ventilation (VE) and carbon dioxide responses during exercise will be used to calculate the VE/carbon dioxide uptake slope. The breathing reserve will be calculated using measured maximal voluntary ventilation (MVV) and the maximal VE using the following equation:

([MVV – VE]/MVV) × 100 **(1)**

The oxygen pulse will be calculated by dividing VO_2_peak (in mL) by the peak heart rate [51].

###### Isometric Strength

Isometric bench press and isometric leg extension will be performed using a custom-built strength ergometer (Gym 2000) with a strain gauge (US2A100 kg, Holtinger) and a custom-made amplifier. The ergometer is specially designed for testing children. In the bench press test, participants will be instructed to push an (upward) static bar with maximal effort for 5 seconds. The participants will lie on the ergometer with the bar height adjusted so that the elbow angle is 90° to get the upper arm in a horizontal position and the lower arm in a vertical position. The participants will be required to maintain the elbow angle throughout the duration of the trial. Each participant will perform at least three trials with 2 minutes of rest between each trial but will be allowed to continue with further trials as long as improvements are observed. The highest value of the trials will be used for later analysis. In the knee extension test, the participant will be seated at the short end of the ergometer bench with his or her back straight, arms down, and hands lightly gripping the seat. During contraction, both hip and knee joint angles will be flexed at 90° (180° will be fully extended), respectively. For the knee extension isometric test, the participants will also perform at least three trials with 2-minute rest between trials but will be allowed to continue with further trials as long as improvement is observed. The best result in each test will be used for later analysis. Hand-grip strength will be measured in the left and right hands (Baseline Life Hand Dynamometer) while the participant will be standing and with the arm extended and pointing down. Each hand will be measured 3 times, with alternating sides, starting with the right hand and approximately 30-second breaks between measurements. The best result for each hand will be used for later analysis.

###### Muscular Endurance

Muscular endurance will be tested using the 1-minute sit-to-stand (STS) test [52]. The participants will perform 1 test trial at least 20 minutes before the final test. The number of repetitions of standing up and sitting down from a chair within 1 minute in the final test will be recorded. In addition, the Borg rating [50] of perceived exertion will be assessed at the end of the test. The test will be performed on a height-adjustable chair to ensure a 90° knee angle. The 1-minute STS test showed high reliability and good criterion-related validity with other exercise capacity tests such as the 6-minute walk test or stair climbing [53-56].

###### Countermovement Jump

All jumps will be performed on a portable force plate (FP4; HUR-Laboratories Oy). Hands will be placed on the hips throughout the test, and the angular displacement of the knees will be standardized so that the participants are instructed to squat down until the knees are bent at approximately 90° and then immediately jump vertically as high as possible, landing back on the force plate on both feet at the same time. The jump height and power will be measured [57]. The best result of at least three attempts will be recorded; however, the participants will be allowed to continue to jump as long as improvements are made. There will be 1 minute of rest between the trials.

###### Blood Volume and Hemoglobin Mass

A known carbon monoxide (CO) dose of approximately 1.2 mL/kg body mass will be administered and rebreathed for 2 minutes. Capillary fingertip blood samples will be collected before the start of the test and 7 minutes after the administration of the CO dose. Both blood samples will be measured a minimum of 5 times to determine the percentage of carboxyhemoglobin using an OSM3 Hemoximeter (Radiometer). Hemoglobin mass will be calculated from the mean change in percentage of carboxyhemoglobin before and after rebreathing CO [58]. Blood volume, plasma volume, and red cell volume will be calculated from hemoglobin mass using venous hemoglobin and venous hematocrit according to Burge and Skinner [59] and Heinicke et al [60].

###### Lung Function

Lung function will be measured using the maximal expiratory flow volume loops. Forced expiratory volume in 1 second, forced vital capacity (FVC), maximal expiratory flow at 50% of FVC (MEF_50_), peak expiratory flow, and the ratio of forced expiratory volume in 1 second to FVC will be recorded. Lung volumes (total lung capacity and residual volume) and airway resistance will be measured using standardized whole-body plethysmography. Diffusion capacity will be measured using the single-breath method, and the result will be adjusted for serum hemoglobin levels. All measurements are according to the American Thoracic Society/European Respiratory Societies guidelines. The Global Lung Function Initiative reference equations will be used, and the outcomes will be expressed as absolute values, percent predicted, and *z* scores and the lower limit of normal.

###### Cardiac Examination

A full functional echocardiography protocol, including 2D, color, pulsed, continuous, and tissue Doppler registrations, will be performed using a GE Vivid E95 ultrasound machine (GE Healthcare) with 4- and 5 MHz 2D probes (4Vc-D or M5Sc). 3D volumes will be acquired as multi-beat fusions with breath hold. The frame rate for 2D images will be kept between 50 and 90 frames per second for 2D strain measurements. Automatic image optimization will be used as the default setting, supplied by manual optimization, as required. Parasternal, apical, selective right ventricular apical, and subcostal views will be applied. For clinical use, left ventricular ejection fraction, as calculated by the Simpson biplane method, fractional shortening by m-mode (MediMatic Compacs software), and peak systolic left ventricular global longitudinal strain (GE EchoPac software), will be reported in addition to any other positive findings of clinical significance. Additional research-based measurements will be performed as the mean value of 3 consecutive cardiac cycles. Left ventricular 4D volumes will be measured using a semiautomatic method (EchoPac Auto-LVQ).

